**5.8.2 Ethnicity, occupation and 4-week quit outcome**

At the end of the study, ethnicity, occupation details and the 4-week quit outcome will be collected from GP practices for all participants.

## Confidentiality

Information obtained throughout the study will remain strictly confidential. All data is stored securely in accordance with the Data Protection Act and the University of Cambridge policy on data security. Electronic data is stored on a secure partition on a University of Cambridge file server. Only the research team will have access to data, with the following exceptions:

1. The text messages are transferred by a company called FastSMS. For participants in the intervention group, the company will have access to name (the first name is used in some of the messages), mobile phone number and the content of the message. The company privacy policy states that all information will remain confidential and will not be disclosed to any third parties.
2. A data processing company might be used to process anonymised data from questionnaire responses. The questionnaires will not contain any identifiable data.
3. ABS laboratories; however the saliva sample they receive will include only the study ID for identification purposes.
4. It is possible that auditors from the funder, sponsor, NHS Trust and regulatory inspectors may require access to the data to check that that the study is being properly conducted.
5. Requests for datasets may be received from outside researchers. If such requests are received at least 3 years after the study has finished (April 2023), they will be considered by the project data committee (CI, trial manager and data manager) and only data with all identifiable personal data removed will be released.

After the study has ended, consent forms and anonymised data may be stored for a minimum of 10 years, to ensure that it has been properly reported. Secure storage will be in accordance with national guidance. Data will be removed and destroyed if participants choose to withdraw from the study and do not wish for their anonymised data to be used.

## Measures

The primary outcome measure is self-reported prolonged abstinence over the whole 6-month follow-up period (allowing for up to five cigarettes in total), combined with 7-day point prevalence with biochemical verification at 6 months to conform to the Russell Standard (West et al, 2005).

Secondary outcome measures include:

1. CO-verified abstinence at 4-week quit date follow-up for at least 2 weeks, assessed by the SCA.
2. Self-reported prolonged abstinence over the whole of the 6-month follow-up period (allowing for up to five cigarettes in total)
3. Self-reported 7 day point-prevalence abstinence at 6-month follow-up.
4. Cost and utility measures: time required to complete iQuit questionnaire; resource use (including use of cessation medication); EQ-5D.

Process measures (all recorded at 6 months) include:

1. number of serious quit attempts lasting at least 24 hours during the 6-month follow-up period.
2. motivation and confidence in quitting.
3. Use of strategies to help avoid smoking or lapsing during the 6-month follow-up period.
4. (intervention group only) evaluation of the tailored advice report and text messaging programme (e.g. how helpful they found them; how they felt about the number of texts sent etc.).

## Statistical analysis

The two groups will be compared using χ2 tests and logistic regression analysis, adjusting for stratifiers and any imbalances in potential confounders between groups. The results will be reported in terms of the absolute difference in percentages or proportions and the odds ratio, with 95% confidence intervals. Analysis will be intention-to-treat, where all those randomised are analysed and participants lost to follow-up assumed to be smoking. We will also conduct sensitivity analyses using a range of less severe assumptions, including a complete-case analysis (Jackson et al, 2014). Deprivation (based on IMD derived from participant’s home postcode) will be examined as a potential moderator of the intervention effect by including a multiplicative term in the logistic regression analysis.

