| **Analysis** | The two groups will be compared using χ2 tests and logistic regression analysis. Results will be reported in terms of absolute difference in percentages or proportions and the odds ratio, with 95% confidence intervals. Analysis will be intention-to-treat, where all those randomised are analysed, and those lost to follow-up assumed to be smoking. Sensitivity analyses will be conducted using a range of less severe assumptions including a complete-case analysis (Jackson et al, 2014) | |

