## Sample size and power calculations

A total of 1452 participants will be recruited for this study. In the iQuit in Practice pilot trial, the quit rates (self-reported prolonged abstinence at 6 months) were 8.9% and 15.1% respectively (Naughton et al, 2014). If we assume a 90% response rate to biochemical verification and that 90% of these are confirmed as non-smokers (figure from StopAdvisor trial supplied by [name], UCL), this gives estimated validated quit rates of 7.1% and 12.1% for control and intervention respectively. An absolute increase of 5% quitting would be a worthwhile and scalable effect for this low cost intervention. Detecting an effect of this size with 90% power using a two-sided chi-squared test at the 5% significance level requires 726 participants per arm (non-responders at follow-up assumed to be smoking; Jackson et al, 2014),1452 in total.

Regular review of rates of follow-up observed the uptake of biochemical validation to be lower than previously estimated. It was calculated therefore that the trial analyses would retain 86% power even when allowing for biochemical validation uptake to be at a lower level of 70%, with an increased sample size of 1700, agreed by the Trial Steering Committee (TSC).

Therefore a total of 1700 participants will be recruited for this study (850 in each arm).

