## Consultation with the Smoking Cessation Advisor following consent to participate

The SCA provides ‘usual care’ to all consenting participants, including advice on smoking cessation, measuring carbon monoxide levels, exploring pharmacotherapy, and supporting the participant to set a quit-date in the next two weeks. Then, in consultation with the participant, the SCA enters answers to the questions on part one of the iQuit Questionnaire which is part of the online CRF. These include cigarettes a day and motivation to quit. The SCA will also input the participant’s Carbon monoxide (CO) level. The CO level is used to characterise the sample and check baseline comparability between the two groups. It will also be used in the tailored advice report for participants receiving the intervention.

Once part 1 of the iQuit questionnaire is completed, the iQuit program will randomise the participant to either the control group or the intervention group. For participants randomised to the control group, no further action is required, and the SCA will conclude the consultation. For those in the intervention group, the SCA will go through part 2 of the iQuit questionnaire with the participant and the iQuit program will use the responses to these questions to automatically generate the tailored advice report, which the SCA will then print and give to the participant. Participants in the intervention group will also begin to receive text messages commencing one day before their quit date. All further consultations from this date will continue routinely for participants in both groups.

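### Covariates beyond the SCA stratifier are chosen by observed baseline imbalance, and neither of the two named tests is said to decide the primary comparison

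*Protocol*

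**What the plan says.** The Statistical analysis section states: "The two groups will be compared using χ2 tests and logistic regression analysis". It continues: "adjusting for stratifiers and any imbalances in potential confounders between groups". The stratifier is known, because Study design stratifies randomisation by SCA. No other covariate is named, and nothing says what counts as an imbalance. Results are to be given as an absolute difference and an odds ratio, without saying whether each is adjusted.

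The Study Synopsis names the same two methods and mentions no adjustment: "The two groups will be compared using χ2 tests and logistic regression analysis. Results will be reported in terms of absolute difference".

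Sample size and power calculations rests on one test only: "Detecting an effect of this size with 90% power using a two-sided chi-squared test at the 5% significance level requires 726 participants per arm".

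The section on the consultation with the SCA has cigarettes a day, motivation to quit and exhaled CO recorded in part 1 of the questionnaire, before randomisation. For baseline CO, the analytic role given is this: "The CO level is used to characterise the sample and check baseline comparability between the two groups". It is not fixed as a covariate.

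**The concern.** Participants are randomised individually with concealed allocation, so any baseline difference between the arms is chance. Choosing covariates because they differ has three consequences.

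- The content of the model is settled only after baseline data have been examined by arm, and with no stated criterion it is open to judgement.
- A variable that predicts quitting strongly but happens to be balanced is left out, although adjusting for it would still help.
- The odds ratio is non-collapsible: its target changes with the covariates in the model. The quantity being estimated would therefore depend on which imbalances occur.

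Naming two tests without ranking them adds a second choice. If the chi-squared test and the adjusted model fall on opposite sides of 5%, the section does not say which answers the trial's question. At stake are the definition of the headline odds ratio and deciding p-value, and a little power.

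**Working it through.** **1. The plan's own figures.** The inputs are from Sample size and power calculations: validated quit rates 7.1% and 12.1%, two-sided 5%, 90% power. With pooled variance and no continuity correction:

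n = [1.960 × √(2 × 0.096 × 0.904) + 1.282 × √(0.071 × 0.929 + 0.121 × 0.879)]² / 0.05² = 728 per arm.

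The protocol states 726. The unpooled formula gives 725, so the figure is reproduced within rounding.

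For the revision, the pilot rates are multiplied by 70% uptake and the 90% confirmation rate:

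- control: 8.9% × 0.70 × 0.90 = 5.61%
- intervention: 15.1% × 0.70 × 0.90 = 9.51%

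With 850 per arm, the power of the unadjusted chi-squared test is 86.2%, against 86% stated. Neither figure includes any gain from covariates, so neither depends on the imbalance clause.

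**2. Performance of the imbalance rule.** The protocol gives no covariate strengths and no imbalance threshold, so these are assumptions:

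- 850 per arm and 4,000 simulated trials per setting;
- six independent standard-normal prognostic covariates, each with log OR 0.2, 0.3 or 0.45 per SD;
- under the imbalance rule, a covariate enters only if its baseline difference has p < 0.05;
- SCA strata not modelled.

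Power at 5.6% vs 9.5% (Monte Carlo SE about 0.5 point):

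| Analysis | log OR 0.2 | 0.3 | 0.45 |
|---|---|---|---|
| Unadjusted chi-squared | 87.7% | 85.9% | 86.7% |
| Logistic, covariates chosen by imbalance | 87.2% | 86.0% | 87.1% |
| Logistic, all six pre-specified | 87.9% | 87.1% | 89.2% |

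The rule admits about 0.3 of the six covariates per trial, as expected from 6 × 0.05, so it behaves like no adjustment. Against it the pre-specified model gains about 0.7, 1.2 and 2 points.

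Type I error with 7.1% quitting in both arms (SE about 0.35 point):

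| Decision rule | log OR 0.2 | 0.3 | 0.45 |
|---|---|---|---|
| Unadjusted chi-squared alone | 5.4% | 5.0% | 4.7% |
| Imbalance-chosen logistic alone | 5.2% | 4.9% | 4.6% |
| Either of these two significant | 5.6% | 5.3% | 5.2% |

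The two tests disagree about significance in roughly 0.5 to 1.7% of simulated trials.

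**3. Events available for handling SCA.** Expected quitters are 850 × 0.0561 + 850 × 0.0951 ≈ 128. Practice recruitment anticipates 66 practices, each with at least one SCA, so there would be about 128 / 66 ≈ 1.9 quitters per SCA, and fewer if practices have several. That is too sparse for one fixed effect per SCA.

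**The case against.** The covariate list, the definition of imbalance and the label of primary test are commonly left to a statistical analysis plan, which is not shown. The power section uses only the chi-squared test, which hints that it decides. The synopsis is a summary, so its silence on adjustment is not a contradiction, and using baseline CO to describe comparability is ordinary practice. The protocol does not call any baseline variable a known predictor of quitting, so any loss from omitting one is assumed.

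Most of this stands, and it limits the size of the point. It does not remove it. The protocol does not merely leave the covariates open: it states a rule for choosing them, and a sound analysis plan would have to overrule that rule rather than fill it in. The hint in the power section is not repeated where the analysis is specified.

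A reader might infer more than the documents support:

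- **Materially inflated type I error.** In the simulation, error of about 5.9 to 6.4% appears when the chi-squared test is paired with a fully adjusted model and the better result is taken. The protocol does not propose that pair. Because it sets no imbalance threshold, trying several would add something: the best of chi-squared and cut-offs of 0.05, 0.10 and 0.20 gave 5.5 to 6.1% across the same covariate strengths, at about 7.6% quitting. That measures misuse of the freedom, not the plan as written.
- **A 40% chance of some spurious imbalance.** This is 1 − 0.95^10. The protocol gives neither ten variables nor a 5% criterion.
- **An underpowered trial.** The 86% reproduces for the unadjusted test. What is forgone is an optional gain.
- **A wholly data-driven model.** The stratifier enters whatever the balance; only the further covariates are open.

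**Conclusion.** The point holds as a fault in a stated rule, with modest numerical consequences. Covariates beyond SCA are selected by chance imbalance, and the deciding analysis is not named.

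Under log ORs of 0.2 to 0.45 per SD, a p < 0.05 imbalance criterion and no modelling of SCA, the rule gives up roughly 1 to 2 points of power against a pre-specified model. Each single test keeps about 5% type I error, and the better of the protocol's two gives about 5.2 to 5.6%. The power figures depend on those assumed strengths. The gain appears as power for the conditional odds ratio, not as a smaller standard error.

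The main harm is that the headline odds ratio and p-value are not defined until the data have been seen by arm. This should be corrected before unblinding; it does not call the sample size or the stated power into question.

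**What to change.** In Statistical analysis, delete the part of the clause that refers to imbalances and name one primary analysis of the biochemically verified 6-month outcome. It should adjust for SCA and for a short list of pre-randomisation variables, fixed before unblinding and kept whatever the observed balance. Candidates are cigarettes per day, baseline CO, motivation to quit, age and IMD. Nothing from part 2 of the iQuit questionnaire should enter, because only the intervention arm completes it, after allocation.

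Handle SCA by a method suited to sparse strata: a random intercept, or conditional or Mantel-Haenszel stratification, rather than one fixed effect per SCA. The simulation above did not test this step.

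Report the unadjusted chi-squared test as supportive, say whether the absolute difference and the odds ratio are each adjusted, and align the Study Synopsis with this section.

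The cost is a few sentences and no new data collection. There are two small downsides: the primary odds ratio becomes conditional on the chosen covariates, and a rule is needed for any missing baseline values.

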## Time and event schedule for participants

| Time / Event | Randomisation  (day 0) | Quit date set by patient* (Day 1 to 14) | Intervening days | 4 weeks after quit date (routine NHS follow-up) | Intervening days | 6 months after randomisation date |
| --- | --- | --- | --- | --- | --- | --- |
| Attend appointment with SCA, at GP practice | X |  |  | X |  |  |
| Written consent obtained to participate in ‘iQuit in Practice’ research study | X |  |  |  |  |  |
| SCA provides ‘usual care’ including CO monitoring | X |  |  | X |  |  |
| Complete on-line iQuit questionnaire with SCA | X |  |  |  |  |  |
| Randomisation to either control or intervention group | X |  |  |  |  |  |
| Receive tailored advice print-out (intervention group only) | X |  |  |  |  |  |
| Participant starts quit attempt |  | X |  |  |  |  |
| Receive tailored text-messages (intervention group only). |  | X  (starting 1 day before quit date) | X | X | X (till 90 days after quit date) |  |
| SCA completes routine 4-week follow-up, as per NHS guidance |  |  |  | X |  |  |
| Follow-up text/email/ questionnaire/telephone call from co-ordinating centre in Cambridge. |  |  |  |  |  | X |
| Saliva sample kit sent to all participants who state prolonged abstinence |  |  |  |  |  | X |

SCA = Smoking Cessation Advisor

* The quit date must be set within the 14 days after randomisation.

Events highlighted in grey are only received by participants randomised to the ‘intervention’ group.

## Sponsor

The ‘Sponsor’ is defined as the “Individual, organisation or group taking on responsibility for securing the arrangements to initiate, manage and finance a study”. The University of Cambridge will act as Sponsor for the trial.

## Study Agreements

Written agreements detailing responsibilities for the trial are signed by parties prior to participant recruitment. These will include the responsibilities of the sponsor, the research team, and the principal investigators, and are initiated by the Research Services Division of the University of Cambridge.

## Study Funding and NHS Cost implications

The research costs for the trial are funded through a 4-year project grant awarded by Cancer Research UK. NHS Service Support Costs include the additional NHS patient-related costs associated with the study. For ‘iQuit in Practice’, this includes the extra time required of NHS staff in order to: attend ‘start-up’ meetings; attend training to undertake the research; identify patients’ eligible to participate; send letters out to patients; explain the study to participants; obtain informed consent; and collect research-specific data.

## Adoption of ‘iQuit in Practice’ onto the UKCRN Clinical Research Portfolio

The iQuit trial has been adopted by the UKCRN and additional NHS Service Support has been sought and approved by the East of England Primary Care Research Network, The study team uploads information on the number of participants recruited to the NIHR CRN accruals database.

## Insurance/Indemnity

The University of Cambridge insurance office has been consulted to ensure that appropriate insurance/indemnity arrangements are in place to meet the potential legal liability of the Sponsor, and investigators/collaborators arising from harm to participants in the design, management and conduct of the research. Since participants are NHS patients, indemnity is provided through NHS schemes or through professional indemnity. GP Practices must check with their providers of insurance that participation in the research is covered for negligent harm.

## Adverse Incident reporting

Since iQuit in Practice does not fall under the Medicines for Human Use (Clinical Trials) Regulations 2004 (as amended), the research team will not collect data on adverse events (AEs), serious adverse events (SAEs) or suspected unexpected serious adverse reactions (SUSARs) as defined by these regulations. However, adverse incidents could still happen, for example;

- breach of confidentiality
- patient complains about aspect of treatment as a study participant
- deviation from study protocol (e.g. recruiting before consent)
- equipment failure
- aggressive behaviour from a participant towards the researcher, practice staff or others.

Adverse incidents relating to the conduct of this research must be reported to the study team within 5 working days of the researcher becoming aware of the incident, using an ‘adverse incident report form’. Incidents of a serious nature may need to be reported to the appropriate study REC.

## Intellectual Property (IP)

The web-based iQuit software has been developed over several years by [name] (University of Cambridge), [name] (University College London) and colleagues. The software is protected by a copyright statement. Further IP advice, regarding protection and commercialisation, will be sought from Cambridge Enterprise (the technology transfer company for the University of Cambridge) as required.

## Research & Development and Research Ethics Committee (REC) approvals

Written approval has been obtained from the Eastern CRN, Cambridge East REC (Ref no: 188824) and the HRA. Any subsequent amendments to study documentation, along with safety, annual progress and final study reports will be submitted to the HRA and REC for information and/or approval, as required. All data will be processed in accordance with the Data Protection Act 1998.

## Patient and Public Involvement

Small focus groups of smokers and ex-smokers assisted with the development of the original iQuit in Practice text message program, and PPI representatives were invited to comment on any revisions prior to study commencement. PPIs will also be consulted on dissemination of the study findings.

## Dissemination of research results

Information on the progress of the iQuit in Practice trial will be publicly available via a number of organisation websites including:

| University of Cambridge PCU site: | http://www.phpc.cam.ac.uk/pcu/ |
| --- | --- |
| UKCRN Portfolio: | http://public.ukcrn.org.uk/search/ |
|  |  |
| ISRCTN Register: | http://isrctn.org/ |

Results of the research will be published in peer-reviewed journals and findings presented to a wide audience, including national and international conferences and other scientific meetings. The 6-month follow-up form will include the opportunity for participants to request a report of the results. A lay summary will be prepared and sent to all participants requesting one.

# Appendix 1: QUIZ questions

**Quiz question**

QUIZ: How many eyes do starfish have? Reply A1 for none, A2 for 4 or A3 for the same number as they have arms.

Response

Incorrect! Starfish have one eye per arm, meaning they vary from 5 to 50 eyes! The eyes aren't anywhere near as good as human eyes, but can see basic images.

Incorrect! Starfish have one eye per arm, meaning they vary from 5 to 50 eyes! The eyes aren't anywhere near as good as human eyes, but can see basic images.

Correct! Starfish have one eye per arm, meaning they vary from 5 to 50 eyes! The eyes aren't anywhere near as good as human eyes, but can see basic images.

no response

Starfish have one eye per arm, meaning they vary from 5 to 50 eyes! The eyes aren't anywhere near as good as human eyes, but can see basic images.

**Quiz question**

How long did it take Neil Armstrong to get to the moon? A1 = 2 days 4 hours and 18 mins, A2 = 4 days 5 hours and 45 mins, A3 = 7 days 16 hours and 12 mins.

Response

Incorrect! It took 4 days 6 hours and 45 mins for Apollo 11 to take Neil Armstrong, Michael Collins and Buzz Aldrin to the moon. They stayed for about 22 hours.

Correct! It took 4 days 6 hours and 45 mins for Apollo 11 to take Neil Armstrong, Michael Collins and Buzz Aldrin to the moon. They stayed for about 22 hours.

Incorrect! It took 4 days 6 hours and 45 mins for Apollo 11 to take Neil Armstrong, Michael Collins and Buzz Aldrin to the moon. They stayed for about 22 hours.

No response

It took 4 days 6 hours and 45 mins for Apollo 11 to take Neil Armstrong, Michael Collins and Buzz Aldrin to the moon. They stayed for about 22 hours.

